## 2. Materials and Methods

### 2.1. Study Design and Setting

This study follows a quasi-experimental design involving two intervention schools undergoing schoolyard greening and two comparison schools without environmental changes. All participating schools are primary schools situated in the Province of Limburg of Belgium and The Netherlands (Figure 1). These provinces are characterized by a low SES, compared to the means of the countries [36,37]. ClinicalTrials.gov identifier (NCT number): NCT04898439. Baseline data collection was completed prior to the start of the intervention, with all baseline measurements conducted in November 2021.

School and subject recruitment. Two schools actively participate in the process of greening the schoolyard (one in Belgium and one in The Netherlands). Two other schools in the nearby region are control schools (one in Belgium and one in The Netherlands). Randomization was not possible due to the necessity for complete voluntary cooperation and participation of the intervention schools in greening the schoolyard. Because participation in the greening intervention required voluntary school commitment and alignment with construction timelines, randomization was not feasible. Therefore, potential confounders at both the child and school level will be measured and adjusted for in the linear mixed models. Baseline measurements were completed in November 2021 (T0). Follow-up measurements were planned each half-year for two years until November 2023 (T6: May 2022, T12: November 2022, T18: May 2023, and T24: November 2023). In The Netherlands, not all measurements could be taken due to practical reasons.

Intervention school recruitment. In early 2021, a newspaper call in The Netherlands recruited nine schools from Limburg to green and diversify their schoolyards. These schools were interviewed, and one was selected to participate as an intervention school on the basis of feasibility criteria and the comparability of the schoolyard size and characteristics. Selection of the Belgian intervention and control school was performed by the ‘Provinciaal Natuurcentrum Hasselt’ based on their call to green schoolyards and make schoolyards more biodiverse the comparableness of the schoolyards and number of enrolled students. The recruitment of the intervention schools was completed in September 2021.

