### 2.9. Number of Participants

Due to the explorative nature of the study (hypothesis generating), no detailed sample size calculations are performed. The aim is to include 150–200 participating children from the participating schools in The Netherlands and Belgium. To account for missing data (assumed to be around 20%), the effective sample size for the analysis might vary between 80 and 120 children (40 to 60 per group). Based on 80% power and a significance level α of 0.05, standardized effect sizes (Cohen’s) between 0.52 and 0.63 can be detected with these expected sample sizes. This study was approved by the commission for Medical Ethics of Hasselt University (CME2021/042) and is a part of the original HPSF trial (METC-Z no. 14-N-142).

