No school-level random effects were added as the number of schools is limited to four (two in Belgium, two in The Netherlands). Since each country only includes one intervention and one control school, including country as fixed factor accounts for the school effect. Distinct statistical methods will address the other research inquiries. Longitudinal effects on numerical quantitative outcome variables will be evaluated employing the identical linear mixed models utilized for the primary outcome. Categorical outcome variables, on the other hand, will be scrutinized through a logistic mixed-model analysis technique (or generalizing estimating equations (GEE)), adopting a model akin to the one delineated for the primary study parameter.

To account for the correlation between repeated measurements several covariance structures (including random effects if necessary) will be considered. The model-fit will be evaluated using the −2log likelihood, where the best covariance structure for the repeated measurements will be chosen based on Akaike’s Information Criterion.

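### The stated 80% power for effects of 0.52 to 0.63 SD holds at a true 5% error rate only if children in the same school are independent, and the sample sizes behind it do not follow from the stated recruitment and loss

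*Protocol article*

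**What the plan says.** Section 2.9 calls the study explorative and reports no detailed sample size calculation, but then gives a quantified one:

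- Recruitment: "The aim is to include 150–200 participating children from the participating schools in The Netherlands and Belgium".
- Loss: "To account for missing data (assumed to be around 20" per cent).
- Analysed: "the effective sample size for the analysis might vary between 80 and 120 children (40 to 60 per group").
- Power: "Based on 80% power and a significance level α of 0.05", standardized effects "between 0.52 and 0.63 can be detected with these expected sample sizes".

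Section 2.1 describes "two intervention schools undergoing schoolyard greening and two comparison schools without environmental changes", one of each kind in each country, without randomization. Section 2.10 says "No school-level random effects were added as the number of schools is limited to four", and argues that country as a fixed factor takes care of the school effect. The limitations in the Discussion mention the modest sample, reduced power and confounding. Nothing in the article mentions correlation between children of the same school or attaches such a condition to the power figure.

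**The concern.** The unit that receives the intervention is the school, but the power figure counts children as if each had been allocated separately. With four schools, any difference between schools that is not due to greening adds to the variance of the group comparison, and recruiting more children per school does not reduce it.

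Two misreadings are at stake. A null result could be taken to rule out effects of about 0.5 to 0.6 SD when the design could have missed them. A nominally significant result from the planned model could be a school difference, because that model's standard error contains no school component. The Discussion says that the study is meant to inform larger research, so the figure may be reused in planning. In addition, the numbers of children on which it rests do not follow from the recruitment target and the loss given in the same section.

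**Working it through.** **Inputs.** From Section 2.9: power 80%, alpha 0.05 (sidedness not stated), n = 40 or 60 per group. From Section 2.1: two schools per arm, so m = n/2 = 20 or 30 children per school if schools are equal in size (assumption). ICC of the analysed outcome: not in the article; assumed 0.01, 0.02 and 0.05.

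**1. The article's own figure.** For independent children, two-sided, the normal approximation is d = (1.960 + 0.842) × √(2/n).

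- n = 40: 2.802 × 0.2236 = 0.627; non-central t with 78 df: 0.634. Stated: 0.63.
- n = 60: 2.802 × 0.1826 = 0.511; non-central t with 118 df: 0.516. Stated: 0.52.

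A one-sided test would give 0.556 and 0.454, which does not fit. The stated values are therefore two-sided, independent-children values, with no room for within-school correlation.

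**2. Does the country term remove the school effect?** Let u be each school's own deviation. The group contrast averaged over countries is

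effect + ½[(u_BE,int − u_BE,con) + (u_NL,int − u_NL,con)] + child-level error.

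The country difference cancels but the four u terms do not, because within each country the two schools differ exactly by group. With total variance 1, the variance of the contrast is ICC + 2(1 − ICC)/n = (2/n) × [1 + (m − 1) × ICC]. The bracket is the usual design effect (DE). The relevant ICC is the one between schools within a country.

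**3. Consequences for the assumed ICCs.**

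- Detectable effect at a true 5% error: 0.634 or 0.516 × √DE. Example, n = 40, ICC 0.05: DE = 1 + 19 × 0.05 = 1.95; 0.634 × 1.396 = 0.89.
- Power of that cluster-corrected test: non-central t, child-level df, non-centrality d√(n/2)/√DE.
- Planned test, which ignores school (normal reference): type I error = 2[1 − Φ(1.960/√DE)]. Nominal power ≈ Φ[(d√(n/2) − 1.960)/√DE]. Same example: 2[1 − Φ(1.404)] = 16%; d√(n/2) = 0.63 × 4.472 = 2.817, and Φ(0.857/1.396) = 73%.

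Each cell shows 40 per group / 60 per group; power is at d = 0.63 / 0.52.

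| ICC | DE | Detectable effect, cluster-corrected | Power, cluster-corrected | Planned test: nominal power | Planned test: type I error |
|---|---|---|---|---|---|
| 0 | 1 / 1 | 0.63 / 0.52 | 79% / 81% | 80% / 81% | 5% / 5% |
| 0.01 | 1.19 / 1.29 | 0.69 / 0.59 | 72% / 70% | 78% / 78% | 7% / 8% |
| 0.02 | 1.38 / 1.58 | 0.75 / 0.65 | 66% / 61% | 77% / 76% | 10% / 12% |
| 0.05 | 1.95 / 2.45 | 0.89 / 0.81 | 51% / 44% | 73% / 72% | 16% / 21% |

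**4. The sample size.** 150 × 0.80 = 120 and 200 × 0.80 = 160. Reaching 80 to 120 needs a loss of 1 − 80/150 = 47% to 1 − 120/200 = 40%, not 20%. With 120–160 children (60–80 per group, 30–40 per school), the independent-children figure is 0.52 to 0.45 (0.516 and 0.446). Applying the design effect at m = 30 and 40:

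- ICC 0.01: 0.516 × √1.29 = 0.59 and 0.446 × √1.39 = 0.53.
- ICC 0.02: 0.516 × √1.58 = 0.65 and 0.446 × √1.78 = 0.59.
- ICC 0.05: 0.516 × √2.45 = 0.81 and 0.446 × √2.95 = 0.77.

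Reconciling the sample size alone would make the stated figure more favourable and leave the independence assumption in place.

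**The case against.** **The cluster-corrected power is not that of the planned test.** This stands. A reader might infer from the 44–72% column that the trial's own analysis has that power. It does not: the planned model has no school term and would reject at about 72–78% at the stated effects. The price is a false-positive rate of about 7–21%, so neither column gives 80% power at 5% error.

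**A school-level test would be harsher still.** A reader might reach for a t test on four schools with 4 − 2 = 2 df. The article supports no such figure. The planned model also fits country, so a school-level version has 4 − 3 = 1 residual df, and no school-level test is planned. I make no use of it.

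**Repeated measures and baseline adjustment may win power back.** This stands as a possibility. Stable school differences partly cancel in change. For illustration, an assumed baseline–follow-up correlation r of 0.5 to 0.7 multiplies the detectable effect by √(1 − r²), that is 0.87 to 0.71. At ICC 0.01 that gives 0.60–0.49 (40 per group) and 0.51–0.42 (60 per group), below the stated values. At ICC 0.05 it gives 0.77–0.63 and 0.70–0.58, at or above them. It is therefore too strong to say that the design can never reach 0.52–0.63. The stated figures use neither device, however: they equal the plain two-sample result.

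**The study is exploratory and admits limited power.** This lowers the stakes. But those statements do not mention clustering, and the 80% figure is printed without a condition.

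**Conclusion.** The point holds as a misstated condition on a printed figure. The sum in Section 2.9 is right for 40 and 60 independent children per group. What fails is its use for four schools exposed as whole units, together with the claim in Section 2.10 that country accounts for school. The 80% power at a true 5% alpha holds only under independence within schools.

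The size of the loss is not known, because it depends on an ICC that the article does not give. Within the assumed 0.01–0.05, equal school sizes and child-level df, the effects detectable at 80% power rise by a factor of √1.19 to √2.45, that is by about 9% to 57%. If the ICC of the adjusted change is close to zero, the stated figures are nearly right. Separately, and without any assumption, 80–120 analysed children contradicts 150–200 recruited with 20% loss. Neither problem shows that the study should not have been done or that more children are needed.

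**What to change.** In Section 2.9:

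1. State that 0.52–0.63 assumes independence of children within schools, and do not give 80% power at alpha 0.05 without that condition.
2. Reconcile the numbers. Either the analysed sample is 120–160 (30–40 per school; 0.52–0.45 SD under independence), or the expected loss is 40–47% rather than 20%.
3. Add a small table of detectable effects at design effect 1 + (m − 1) × ICC for ICC 0.01, 0.02 and 0.05, using the reconciled m. Label it cluster-corrected and the ICCs as assumed. One sentence should say that an analysis without a school term would exceed the 5% error rate if the ICC is above zero.

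The cost is a few sentences and a table. No enrolment, data collection or model has to change. The only downside is a less favourable stated figure.

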### 2.10. Data Analysis

Linear mixed model analysis will be employed to evaluate the longitudinal impact of the intervention on the primary outcomes, absolute BMI Z-scores, change in cognitive function, change in well-being, and change in black carbon levels. Data will be analyzed using linear mixed models, performed in IBM SPSS Statistics for Windows (version 28.0.1.1, Armonk, NY, USA: IBM Corp). This approach addresses correlations within individuals inherent in repeated-measures research designs. Its advantage lies in handling missing values naturally through a likelihood-based method, assuming data are missing at random.

The fixed part of the model incorporates group (intervention vs. control), time (measurement time points), the interaction term group*time, and country (Belgium/The Netherlands). Baseline variables linked to missing data or outcomes will also be included for unbiased and precise results. To account for the correlation between repeated measurements several covariance structures (including random effects if necessary) will be considered. The best covariance structure for the repeated measurements will be chosen based on Akaike’s Information Criterion. The analysis will encompass all participants with at least one outcome measurement. Because several measurements were collected only in Belgian or only in Dutch schools, the resulting missingness is structured and not at random. Linear mixed models are used because they accommodate unbalanced data and allow all available observations to be included without listwise deletion. Country will be included as a fixed effect in all models to control for systematic differences between the Belgian and Dutch school contexts. For outcomes collected in only one country, analyses will be conducted within that specific subsample and reported separately. In addition, sensitivity analyses will be performed to examine whether excluding country-specific measures affects the direction or magnitude of findings for outcomes measured in both countries.

No school-level random effects were added as the number of schools is limited to four (two in Belgium, two in The Netherlands). Since each country only includes one intervention and one control school, including country as fixed factor accounts for the school effect. Distinct statistical methods will address the other research inquiries. Longitudinal effects on numerical quantitative outcome variables will be evaluated employing the identical linear mixed models utilized for the primary outcome. Categorical outcome variables, on the other hand, will be scrutinized through a logistic mixed-model analysis technique (or generalizing estimating equations (GEE)), adopting a model akin to the one delineated for the primary study parameter.

To account for the correlation between repeated measurements several covariance structures (including random effects if necessary) will be considered. The model-fit will be evaluated using the −2log likelihood, where the best covariance structure for the repeated measurements will be chosen based on Akaike’s Information Criterion.

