Control school recruitment. The schools that voluntarily agreed to participate were selected on the basis of the following inclusion/exclusion criteria: a high pavement-to-greenery ratio and a location in the proximity of the intervention schools with comparable populations and SES backgrounds.

Subject recruitment. Children were recruited for the baseline measurement through informational brochures sent via mail and reminders from the school staff. Furthermore, the research team visited all classrooms to provide information about the study and encourage participation. All children aged 7–12 from both intervention and control schools were eligible for inclusion in this study. Before the baseline examination, written consent from the parents was obtained and children gave their oral permission to participate. The enrollment of children for the initial measurement was concluded in November 2021.

Intervention. Both intervention schools underwent a greening procedure increasing biodiversity, in which they adjusted the gray schoolyard into a green biodiverse schoolyard consisting of (i) the creation of adventurous and diverse play areas, (ii) the establishment of green rest areas, (iii) the planting of flowers, shrubs, hedges and/or trees, and/or (iv) variation in activity zones such as farm animals, pools or vegetable gardens.

Because the greening intervention was implemented by two different schools and included varying components, such as water features, gardens, and diverse vegetation, some heterogeneity in intervention intensity is expected. As each country (Belgium and The Netherlands) includes one intervention and one control school, the correction for country as fixed factor captures unmeasured differences between schoolyards.

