### 2.2. Outcome Parameters

Table 1 shows an overview of all outcome measures collected in children and parents/caregivers. The administration of questionnaires that were completed by the children were taken collectively during regular classes. The children independently read and completed the questionnaires. Throughout this process, at least one researcher was present to oversee and address any queries. The anthropometric measurements were taken individually. Tailored questions, accompanied by various graphical illustrations, were utilized in the lunch and general questionnaire. The cognitive performance of children was assessed during regular classes in a separate room. To prevent excessive burden on children and school staff, the majority of child-related measurements were scheduled within a regular school week.

Personal characteristics questionnaire. The parents filled out a questionnaire before the baseline examination to collect information about parental education, parity, ethnicity, parental occupation, income, household smoking behavior, illness, socio-economic demographics, birth date of the child, sex of the child, and the use of medication. Completion of privacy-sensitive questions, such as parental BMI, socio-economic status, and disease status, were optional.

Strengths and Difficulties Questionnaire (SDQ). At each examination, a parent completed the Strengths and Difficulties Questionnaire (SDQ) to assess the child’s emotional and behavioral well-being [38]. The validated SDQ includes five subscales: emotional symptoms, conduct problems, hyperactivity/inattention, peer relationship problems, and prosocial behavior. The first four subscales contribute to a total difficulty score, with lower scores indicating fewer social-emotional difficulties. Responses are scored on a three-point scale (0–2).

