## Figures and Tables

**Figure 1 ijerph-22-01805-f001:**
[figure not shown]
Map of Intervention and Control School Locations in the Study Region.

**Table 1 ijerph-22-01805-t001:** Overview of questionnaires and measurements for data collection measures within the Green Healthy Elementary School of the Future initiative.

Data Collection Activity	Parents	Children	Time Point
General questionnaire			
Personal data (birth data, sex, ethnicity, addresses, parity, SES, education level of the parents)	x		T0
Sleep ^1^	x		T0, T6, T12, T18
School absenteeism ^1^	x		T0, T6, T12, T18
Household smoking habits	x		T0, T6, T12, T18, T24
Visits to GP, disease status ^3^	x		T0, T6, T12, T18
Quality of life (parental PedsQL) ^1^	x		T0, T6, T12, T18
PA behavior	x		T0, T6, T12, T18
Food + water consumption, habits and preferences ^1^	x	x	T0, T6, T12, T18
Strengths and difficulties questionnaire (SDQ)	x		T0, T6, T12, T18, T24
Kidscreen-52		x	T0, T6, T12, T18, T24
Physical Activity Questionnaire for Children (PAQ-C)		x	T0, T12, T18
Bullying behavior		x	T0, T6, T12, T18, T24
Knowledge, perception and valuation of biodiversity		x	T0, T12, T18, T24
Height		x	T0, T12, T18, T24
Weight		x	T0, T12, T18, T24
Waist/hip circumference		x	T0, T12, T18, T24
Physical activity using Accelerometer (Actigraph, GT3X+, Actigraph, Pensacola, FL, USA) ^2^		x	T0, T12, T18
Cognitive tasks and eye-tracking		x	T0, T6, T12, T18, T24
Particulate matter determination in urine ^3^		x	T0, T6, T12, T18, T24

^1^ Measurements only performed in Dutch schools. ^2^ Measurements only performed in intervention schools. ^3^ Measurements only performed in Belgian schools. Due to practical reasons T6 and T24 measurements could not be performed in Dutch primary schools. T0: November 2021, T6: May 2022, T12: November 2022, T18: May 2023, and T24: November 2023.

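### Siblings can enrol and would share an arm, but the stated models allow only for within-child correlation; if siblings change alike, the group-by-time standard error is somewhat too small

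*Protocol article*

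**What the plan says.** All references are to the Protocol article.

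- **Who can enter.** Section 2.1, under subject recruitment: "All children aged 7–12 from both intervention and control schools were eligible for inclusion in this study". Parental consent was required. No rule restricts enrolment to one child per family.
- **Dependence in the model.** Section 2.10 says of the mixed model: "This approach addresses correlations within individuals inherent in repeated-measures research designs". Covariance structures and optional random effects have the same purpose: "To account for the correlation between repeated measurements several covariance structures (including random effects if necessary) will be considered".
- **Fixed part.** "The fixed part of the model incorporates group (intervention vs. control), time (measurement time points), the interaction term group*time, and country (Belgium/The Netherlands"), with baseline variables related to missingness or outcome added.
- **Levels above the child.** Only school is discussed, and it is set aside: "No school-level random effects were added as the number of schools is limited to four". Family and class are not mentioned.
- **Reach of the model.** "Longitudinal effects on numerical quantitative outcome variables will be evaluated employing the identical linear mixed models utilized for the primary outcome". Categorical outcomes get a similar logistic mixed model or GEE. The structure therefore also covers the Strengths and Difficulties Questionnaire (SDQ), for which section 2.2 says that "a parent completed the Strengths and Difficulties Questionnaire (SDQ) to assess" the child's well-being at each examination.
- **Data that could link siblings.** Table 1 lists, at T0, "Personal data (birth data, sex, ethnicity, addresses, parity, SES, education level of the parents").

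**The concern.** Section 2.10 does more than stay silent on clustering. It says which correlation the model handles, looks one level up, and stops at school. Followed as written, it treats two siblings as independent children.

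Siblings at one school are always in the same arm, so positive correlation between them adds to the variance of the arm contrast and does not cancel. Two routes are plausible. Children in one household share a home diet, which may move BMI z-score and food intake together. One parent may also rate several children on the SDQ, and a drift in that parent's standards would shift all those ratings at once. Siblings usually sit in different grades, so a class or grade term would not absorb this.

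At stake are intervals that are too narrow and a false-positive rate above the nominal 5% for the group-by-time effect, which carries the intervention comparison.

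**Working it through.** **1. The plan's own figure.** Section 2.9 gives 40 to 60 analysed children per group, 80% power, α = 0.05 and detectable standardized effects of 0.52 to 0.63. Sidedness is not stated; two-sided reproduces the figures. For independent children, d = (1.96 + 0.84) × √(2/n):
- n = 60: normal approximation 0.51, t-test 0.516.
- n = 40: normal approximation 0.63, t-test 0.634.

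The stated range therefore rests on independent children.

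**2. Effect of sibling pairs.** Let s be the share of analysed children in same-school pairs and ρ the sibling correlation of the analysed quantity (here, change). Then
- design effect = 1 + s × ρ;
- true SE ÷ model SE = √(design effect);
- actual type I error = 2 × [1 − Φ(1.96 ÷ √(design effect))].

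Neither s nor ρ is in the document. Both are assumptions, shown as a range:

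| s | ρ of change | Design effect | True SE ÷ model SE | Type I error |
|---|---|---|---|---|
| 0.10 | 0.2 | 1.02 | 1.010 | 5.2% |
| 0.20 | 0.3 | 1.06 | 1.030 | 5.7% |
| 0.30 | 0.5 | 1.15 | 1.072 | 6.8% |
| 0.40 | 0.5 | 1.20 | 1.095 | 7.4% |
| 0.50 | 0.5 | 1.25 | 1.118 | 8.0% |

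For detectable effects, the lowest row gives 0.52 × 1.010 = 0.53 and 0.63 × 1.010 = 0.64. The highest gives 0.52 × 1.118 = 0.58 and 0.63 × 1.118 = 0.70.

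**3. Simulation.** With no true effect and a t-test on change, 40,000 runs gave these rejection rates:
- s = 0.2, ρ = 0.3: 5.8% at 40 per arm, 5.6% at 60.
- s = 0.5, ρ = 0.5: 7.8% at 40 per arm, 8.2% at 60.

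These agree with the formula. The test is a simplification of the planned repeated-measures model.

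**4. Level versus change.** With 50 per group, s = 0.2 to 0.4, a sibling correlation of 0.5 in level and none in change, the contrast in change was rejected in 4.9–5.1% of 20,000 runs, which is nominal. With a correlation of 0.5 in change as well, the rate was 6.1–7.2%. The inflation comes from correlated change.

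**5. Information on a family effect.** The number of pairs is s × N ÷ 2. At s = 0.10 and N = 80 that is 4; at s = 0.50 and N = 120 it is 30. So 4 to 30 pairs, over both arms together, would inform a family variance. Counting single children as their own family, the number of families is N minus the number of pairs, between 80 − 20 = 60 and 120 − 6 = 114.

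**The case against.** The strongest reply has four parts.

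- **Sibling enrolment is inferred.** The article never says that siblings took part, or how many. A pair counts only if both are aged 7–12, have consent and are analysed. A reader might infer that siblings certainly entered together and that the standard errors are therefore too small. The document does not support that: the eligibility rule makes sibling enrolment likely, and the bias follows only if it happened and changes correlate. This part stands, and the point is conditional for that reason.
- **Shared homes mostly create similarity in level.** A stable rating habit or household background cancels in change, and baseline covariates may absorb part of it. This also stands for complete data. It does not remove correlated change, such as a shift in home diet or rater drift. Data are also incomplete by design, since the Dutch schools have no T6 or T24, so level correlation may leak slightly into the contrast; that was not quantified.
- **An article may leave sibling handling to a fuller document.** Silence alone would be no finding. Here the text states the dependence structure, gives its purpose and discusses the level above the child, so the omission is part of the model as described.
- **Little hangs on it.** The study is exploratory and non-randomized, with two schools per arm and no school term. A family term does not cure school-level dependence. That limits the gain, but the article's reason for omitting school, too few units, does not carry over to 60 or more families.

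A reader might also infer that parent-rated outcomes suffer most. A shared rater makes this plausible, but no figure in the document shows it.

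**Conclusion.** The point holds conditionally. The plan as written treats same-arm siblings as independent. If siblings are enrolled and their changes correlate, the group-by-time standard error is understated. On assumed shares of 10–50% in pairs and correlations of change of 0.2–0.5, the true standard error is about 1–12% above the model's and the type I error about 5.2–8.0%. The lower end is negligible and the upper end moderate. If siblings are alike only in level, the contrast keeps essentially its nominal error with complete data. All of this comes in addition to the unmodelled school-level dependence, which is a separate matter. It is a cheap improvement and no threat to the study's main conclusions.

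**What to change.** 1. Build a family identifier from the addresses and parent forms already collected, and report the number of sibling sets by arm and country.
2. State in section 2.10 that the child-level models, including the primary BMI z-score model, cluster on family. Family-clustered robust standard errors are the simplest route for the linear mixed models and keep their likelihood-based handling of missing values. Where GEE is used for categorical outcomes, make family the cluster.
3. A family random intercept is an alternative. Add a family-by-time term only where it is estimable. With perhaps 4 to 30 pairs it often may not be, and an intercept alone does not address correlated change.
4. If these models do not converge, run a sensitivity analysis with one child per family.

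**Cost.** A linkage step in data management, one extra modelling specification and slightly wider intervals. The one-child-per-family analysis drops one child per pair, so 4 to 30 children under the assumptions above. If few siblings are found, results will barely change and the assumption will have been checked.

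### Four schools cannot give the promised adjustment for school-level confounders, and the stated covariate rule does little to protect the group-by-time estimate

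*Protocol article*

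**What the plan says.** Section 2.1 of the protocol article describes the design: "This study follows a quasi-experimental design involving two intervention schools undergoing schoolyard greening and two comparison schools without environmental changes". Each country contributes one school of each kind. From the lack of randomisation the article concludes: "Therefore, potential confounders at both the child and school level will be measured and adjusted for in the linear mixed models". The Intervention paragraph of the same section adds that the country term takes up schoolyard differences that were not measured.

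Section 2.10 sets out the model: "The fixed part of the model incorporates group (intervention vs. control), time (measurement time points), the interaction term group*time, and country (Belgium/The Netherlands"). It then adds: "Baseline variables linked to missing data or outcomes will also be included for unbiased and precise results". The only interaction listed is group by time; no covariate-by-time term appears. On schools it says "No school-level random effects were added as the number of schools is limited to four (two in Belgium, two in The Netherlands"), followed by "Since each country only includes one intervention and one control school, including country as fixed factor accounts for the school effect".

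Section 2.1 also records design features that bear on confounding. Control schools were chosen for "a high pavement-to-greenery ratio and a location in the proximity of the intervention schools with comparable populations and SES backgrounds", and T0 preceded the intervention. The Discussion lists possible confounding as a limitation.

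**The concern.** In a four-school comparison without randomisation, the main threat is that the greened schools differ from their comparators in ways that affect how children change: intake, staffing, other health programmes, neighbourhood. The Methods tell the reader that such differences are handled twice over, by school-level covariates and by the country term. If neither can do this, a difference in trend between two pairs of schools may be read as an effect of greening.

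The covariate rule raises a related question. The effect of interest is the group-by-time term, and the rule as stated may not touch it.

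**Working it through.** **Plan's own figure.** The article gives no figure on this point. The nearest is the detectable effect of 0.52 to 0.63 in Section 2.9. With two-sided alpha 0.05 and 80% power, (1.96 + 0.84) x sqrt(2/n) gives 0.63 at n = 40 and 0.51 at n = 60 per group (0.634 and 0.516 with the t-test). The figure reproduces, and nothing below depends on it.

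**1. Between-school degrees of freedom.** Inputs: four schools (Section 2.1); intercept, group and country in the model (Section 2.10). Written as (intercept, group, country), the schools are (1,1,0), (1,0,0), (1,1,1) and (1,0,1). This matrix has rank 3, so 4 - 3 = 1 remains.

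**2. Adding school-level covariates.** Let D_B and D_N be the intervention-minus-control outcome gaps in Belgium and The Netherlands, and S_B and S_N the same gaps in a school variable. With intervention effect b and covariate effect c:

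- D_B = b + c x S_B
- D_N = b + c x S_N

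This is two equations in two unknowns, so one school variable fits the school means exactly and leaves nothing over. If S_B = S_N, the equations cannot be solved for b and c. Two or more variables give at least three unknowns. The rank check agrees:

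| School covariates | Columns | Rank |
|---|---|---|
| 0 | 3 | 3 |
| 1 | 4 | 4 (saturated) |
| 1, same gap in both countries | 4 | 3 (aliased) |
| 2 | 5 | 4 |
| 3 | 6 | 4 |

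The same count holds if D_B and D_N are gaps in change from baseline.

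**3. What country removes.** A country effect moves both schools in a country by the same amount, so it cancels from D_B and from D_N. Whatever separates the two schools within a country stays in those gaps, and hence in the group contrast.

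**4. Single-country outcomes.** Table 1 restricts urinary black carbon to Belgium, and Section 2.10 analyses such outcomes within that country. Two schools with intercept and group leave 2 - 2 = 0, so group and school are the same variable. The Dutch-only outcomes have the same count. Table 1 also says that T6 and T24 were not done in Dutch schools, so the observed T24 data, including BMI, come from one intervention and one control school.

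**5. Baseline main effects and group by time.** Take two time points and complete data. A covariate x entered only as a main effect adds the same amount at both times and drops out of each child's change. The group-by-time estimate is the difference in mean change, so it does not move.

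A simulated example (one data set, ordinary least squares) had 100 children, 50 per group. The mean of x was 0.5 higher in the intervention group, and x had an effect of 0.3 on change. The true group-by-time effect was 0, so the expected confounding is 0.5 x 0.3 = 0.15.

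| Covariate terms | Group-by-time estimate |
|---|---|
| none | 0.152 |
| x | 0.152 |
| x and x-by-time | -0.033 |

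Only the time interaction brought the estimate near zero. Country, as a time-constant main effect, behaves like x in the second row.

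**The case against.** The strongest reply is that the design has other protection. Control schools were sought nearby with similar populations and socio-economic background. The Belgian pair was chosen for comparable schoolyards and enrolment. T0 came before the greening, and group plus group by time removes stable differences between groups. This stands: a reader might infer that covariate adjustment is the plan's only defence against confounding, and the article does not support that. These features do not deal with differing trends.

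A reader might also infer that covariates will be screened by significance in the trial data, so that real confounders are dropped and standard errors ignore the selection. Section 2.10 says only that the variables are linked to outcomes or missingness. It gives no test or cut-off, and the choice could rest on prior knowledge. A confounder must relate to the outcome, so an outcome-linked rule can catch it. Which variables enter is commonly left to a statistical analysis plan, which is not shown. That inference is not part of this point.

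Nor is it right that no school variable could ever be entered. One that is not aliased can be, at the price of saturation.

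Finally, the study is called exploratory and the Discussion concedes possible confounding. That tempers the consequence, but the Methods still say the school effect is accounted for.

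**Conclusion.** The point holds in two parts.

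First, the school-level adjustment described in Section 2.1, and the role given to country in Sections 2.1 and 2.10, are properties that the design does not have. One between-school degree of freedom remains across four schools, and none for single-country outcomes. School-level confounding, above all differing trends, cannot be separated from the intervention. This follows from the number of schools, so no unseen analysis plan could repair it.

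Second, the covariate rule as stated does little for the group-by-time estimate. This rests on reading the added baseline variables as main effects, since no time interactions are listed, and it is exact only for balanced complete data. With the missing Dutch time points and the roughly 20% missing data assumed in Section 2.9, main effects could shift the estimate somewhat. The size of any real bias cannot be derived from the article; the 0.152 illustrates the mechanism and does not forecast it.

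No sample-size figure changes. The text should be corrected because it bears on what the trial may conclude.

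**What to change.** - In Section 2.1, delete the reference to school-level adjustment.
- In the Intervention paragraph of Section 2.1 and in Section 2.10, say that country removes only what the two schools in a country share.
- State that school-level confounding is not removed, and limit the conclusions accordingly.
- In the individual-level models, use one child-level set already collected at T0, for example age, sex, parental education or SES, and ethnicity. Include covariate-by-time interactions in every case, not only where baseline imbalance is seen. Age and sex may add little for BMI Z-score, which is computed from reference values, but a single set keeps the models consistent.
- Section 2.2 makes the SES items optional, so handle their missing values by imputation.
- Do not adjust black carbon for school-mean household smoking: with two schools it is aliased with group.

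The cost is rewording in two sections, a few model degrees of freedom, an imputation step and a more cautious claim. No new data are needed.
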